#### Mechanistic study related risks

For anocortical tests, the patient must be able to submit for a pre-study registration MRI, have a plug anal electrode inserted and sit in the MEG scanner for a total of about 45 min; the patient must attend three times. These tests are non-invasive and only confer mild discomfort due to insertion of anal catheter. No ionising radiation is employed by any tests.

For the anorectal tests, the main difference from routine clinical evaluation of anorectal function is the addition of prolonged high-resolution anorectal manometry. This test is not performed routinely and has a longer duration than standard studies (about 110 min); the patient must attend twice. These tests are non-invasive and only confer mild discomfort due to insertion of anal catheter. No ionising radiation is employed by any tests.

#### Study benefits

Participants will receive a high standard of surgery using the latest technical optimisation and monitored care as consequence of the protocol. All participants will receive SNM therapy due to the crossover design. Participation will add to the knowledge base for determining the pathophysiology of disease and treating adults with FI.

### Dissemination

Scientific findings will be subjected to international reporting and peer review. We will direct this information to the following groups: study participants and carers who have been involved in the trial; charity links and patient groups; NIHR collaboration.

## Discussion

### Double-blind efficacy study

A double-blind, randomised crossover design is appropriate to experimentally assess clinical effect size and to study mechanism. The crossover will compare sub-sensory chronic sacral-root stimulation against SHAM stimulation with the well acknowledged advantage of statistical efficiency. It is, however, also acknowledged that such a study *must* improve on the previous four attempts at crossover studies to provide useful efficacy data. The proposed design will address the main criticisms of previous studies:Adequate intervention periods to adequately assess response. We will have two 16-week periods (SNM and SHAM) in comparison with previous studies (maximum 1 month [15])Adequate washout period and reduced risk of carryover effects. While the duration of carry over effects of SNM is unknown, the current study design allows for almost 3 months’ washout before outcomes are assessed, compared to a maximum in previous studies of 1 week [15]. Clinical experience suggests that this duration is adequate but we will, nevertheless, continuously monitor the kinetics of therapy and washout throughout the study using the newly developed e-recording toolsAdequate statistical power, we propose a completed crossover of 80 patients compared to previous maximum of 24 [15]Reduced selection bias. Although the crossover design does not permit full adherence to an ITT principle; i.e. from start of trial therapy with test stimulation, we will randomise all newly implanted patients rather than patients who have already been selected on the basis of successful chronic therapy. Selected patients will thus be naïve to chronic stimulation and *all* consenting implanted patients will be randomisedReduced attrition bias. We will continue assessments on all participants provided that the patient has not withdrawn consent. Patients who become unblinded to intervention would not, however, contribute data to analysisImproved patient blinding. We will use the experience gained from the Durham-based NIHR RfPB TiLTS-CC study to maintain blindingImproved assessment methods (e.g. diaries are collected for a longer period. As well as a paper diary an electronic simple touch-screen device will also be trialled)

We do, however, accept that the choice of design has some limitations:Although it is acknowledged that a small proportion of patients prefer supra-sensory stimulation (about 10% in our clinical practice), especially in the short term, for double-blinding it is clearly necessary to mandate sub-sensory stimulation and we acknowledge that this is in effect an experimental variant of the therapy used in ‘real life’. We will, however, comply with routine clinical practice by having a reprogramming session at 6 weeks in each arm regardless of intervention status; i.e. in the SHAM arm this will be a ‘pseudo-reprogramming’ event. For the FI indication, a recent randomised observer-blinded comparison showed no difference in effects of supra- and sub-sensory stimulation [27] building on a small study that showed that therapeutic response threshold was significantly lower than sensitivity threshold [36]. However, we acknowledge that some differences in physiological results have been recorded for sub- and supra-sensory stimulation in the patients with slow-transit constipation [37] and this is acknowledged in the study titleWe acknowledge that it is difficult (and labour intensive) to blind patients to SNM in crossover designs, particularly for patients who receive the intervention first and then have it switched to OFF. This proved a problem in a recent study of irritable bowel syndrome [38] in which 75% patients correctly identified that the stimulator was ON or OFF across all crossover phases. This noted, previous crossover studies of FI (accepting limitations in published documentation) have successfully blinded participants. This remains a risk for any placebo-controlled intervention where the number needed to treat is relatively small; i.e. the majority of patients can identify their stimulation status by the effect it has on their symptoms. This noted, the effect size of SNM vs. SHAM remains uncertain (a reason for performing the study)The study does not address the long-term clinical effectiveness, cost-effectiveness and safety of SNM

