**Methods/design:**

The design encompasses a multicentre, randomised, double-blind crossover trial and cohort follow-up study. Ninety participants will be randomised to one of two groups (SNM/SHAM or SHAM/SNM) in an allocation ratio of 1:1. The main inclusion criteria will be adults aged 18–75 years meeting Rome III and ICI definitions of FI, who have failed non-surgical treatments to the UK standard, who have a minimum of eight FI episodes in a 4-week screening period, and who are clinically suitable for SNM. The primary objective is to estimate the clinical efficacy of sub-sensory SNM vs. SHAM at 32 weeks based on the primary outcome of frequency of FI episodes using a 4-week paper diary, using mixed Poisson regression analysis on the intention-to-treat principle. The study is powered (0.9) to detect a 30% reduction in frequency of FI episodes between sub-sensory SNM and SHAM stimulation over a 32-week crossover period.

Secondary objectives include: measurement of established and new clinical outcomes after 1 year of therapy using new (2017 published) optimised therapy (with standardised SNM-lead placement); validation of new electronic outcome measures (events) and a device to record them, and identification of potential biological effects of SNM on underlying anorectal afferent neuronal pathophysiology (hypothesis: SNM leads to increased frequency of perceived transient anal sphincter relaxations; improved conscious sensation of defaecatory urge and cortical/subcortical changes in afferent responses to anorectal electrical stimulation (main techniques: high-resolution anorectal manometry and magnetoencephalography).

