The Model 8840 Clinician programmer is able to access log data of stimulation usage so there is potential to check all data on ON-OFF cycling during the study intervention periods if this is required to validate fidelity of the intervention (a bit like used blister-packs to count unused drugs in a drug trial). During the SHAM period the neurostimulator will be active but not be providing stimulation (current set to 0 V). Therefore, analysis of neurostimulator activity in the SNM and SHAM phases should be equivocal in percentage of neurostimulator ‘use’ and un-blinding one participant would not compromise blinding for the remainder. The digital programming unit (N’Vision Clinician Programmer Model 8840) will not be supplied to the patient but can be used post hoc to determine if the patient has changed settings or switched stimulation on or off during the study (the programmed settings will also have been recorded on a case report form (CRF) by the unblinded clinical team member). The patient will not be removed from the study if the tamper-proof tape has been broken. This will be recorded for statistical analysis.

A nominated member of the research team or normal care clinician will have access to the programmer at the relevant fixed time points for stimulator adjustment (crossover and 6-week reprogramming). This person who will not be blind to intervention status will not otherwise be involved in the research protocol; e.g. outcomes assessments, collection of CRFs, data management.

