### Withdrawal criteria

Patients can withdraw at any point in the study. The data collected from consent to the point of withdrawal will be kept for the ITT analysis, as outlined in the patient information and consent form.

Patients will be withdrawn from treatment but follow-up data will be continued to be collected if they:Electively withdraw from treatmentAre not fit for surgeryBecome pregnant or intend to become pregnantAre unable to participate due to an concurrent severe illnessDevelop an acute psychological illness causing concerns

Patients will be withdrawn from both treatment and follow-up if they:Choose to withdraw from treatment and follow-up data collectionBecome lost to follow-up (after at least three attempts at contact by research/clinical staff using at least two different methods)Die or become severely incapacitated so follow-up data collection is impossible

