### Outcomes

#### Primary clinical outcome

The reduction in FI events in SNM vs. SHAM phase of crossover (16 and 32 weeks).

Frequency of FI episodes per unit time will be patient-recorded using 4-week paper bowel diaries. While the limitations of this method are well established [29], this remains the ‘gold standard’ in FI [15, 18, 27, 30] (we will, however, be recording for 4 weeks rather than only 2 as in many previous studies). The measure of treatment effect is the average number of FI events per 4-week period for patients undergoing SNM as compared with the average number of events for patients undergoing SHAM simulation. The study is powered to detect a ratio of 0.7. This is not to be confused with the reduction in the actual number of events post intervention for a given patient, where a 50% reduction has frequently been employed, albeit subjectively, to define ‘success’ for that patient [18, 30]. Rather, we use number of events as a quantitative outcome, achieving greater power than a dichotomous outcome of successful/unsuccessful, and we power to detect a 30% reduction, on average, in this outcome on ITT principles.

The paper diary will be completed prior to implantation then at the end of each crossover phase and again at the end of the cohort follow-up.

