#### Method of analysis

##### Efficacy: primary analysis from crossover study

This analysis will be completed by the statisticians at PCTU.

The analysis of the primary outcome will compare SHAM and active therapy in both arms of the crossover trial, at T12–T16 and T28–32, using mixed Poisson regression analysis to adjust for a fixed effect of period and a random effect of individual. To allow observed numbers of events before and after activation in the same individual to have an over-dispersed Poisson distribution we will also include a random effect of time within individual. We will analyse all non-missing data, adjusting for the stratification variables (random effect of centre and fixed effect of sex). This approach is unbiased if missingness is related to observed outcome data or stratification factors from the same participant (a ‘missing at random’ assumption): further sensitivity analyses will explore this assumption if needed.

Secondary outcomes will be analysed in the same way – using Poisson regression for outcomes that are counts, and linear regression for other quantitative outcomes.

Exploratory analyses may also be performed using geospatial data from the touch-screen devices to calculate, e.g. number of outings from primary residence, as well as distance travelled and velocity (a surrogate for mode of transport), and to produce numerical and graphical summaries aggregated by trial arm.

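### The Discussion excludes unblinded participants from analysis, which contradicts the intention-to-treat primary analysis and may bias the SNM/SHAM ratio towards 1

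*Protocol article*

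**What the plan says.** The exclusion appears once, in the Discussion under Double-blind efficacy study, in the item on reducing attrition bias: "Patients who become unblinded to intervention would not, however, contribute data" to the analysis.

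The parts of the article that define the analysis say otherwise:

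- Abstract, Methods/design: the primary objective is assessed "using mixed Poisson regression analysis on the intention-to-treat principle".
- Primary clinical outcome: "we power to detect a 30% reduction, on average, in this outcome on ITT principles".
- Efficacy: primary analysis from crossover study: "We will analyse all non-missing data, adjusting for the stratification variables". No exclusion for unblinding is mentioned.
- Withdrawal criteria: "The data collected from consent to the point of withdrawal will be kept for the ITT analysis".

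On how unblinding might arise, the Discussion names as a risk that "the majority of patients can identify their stimulation status by the effect it has on their symptoms". It also says that earlier crossover studies in faecal incontinence blinded participants successfully.

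**The concern.** The article describes two different analysis sets for its primary outcome. An analyst following the Discussion would drop participants whom an analyst following the analysis section would keep.

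The exclusion depends on something that happens after randomisation and that treatment may cause. If a participant works out the allocation because symptoms changed between periods, removing that participant removes a large treatment contrast. The missing-data argument does not cover this. It reads "This approach is unbiased if missingness is related to observed outcome data or stratification factors from the same participant", and so relies on the participant's own observed outcomes staying in the model. Excluding the participant takes those outcomes out.

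The term is also left open. Becoming unblinded could mean a formal code break, seeing the setting, feeling stimulation, or guessing correctly. Participants' perceived allocation is collected as a secondary outcome, so without a definition the rule could be extended to correct guesses after the data are seen.

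**Working it through.** **Inputs (Sample size and Primary clinical outcome sections).** SD of log(events) 0.775; within-person correlation 0.2; target ratio 0.7; significance level 5%, taken as two-sided; power 90%; 80 evaluable; 90 randomised after 10% loss to follow-up.

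**Step 1: reproduce the plan's figure.** Paired normal approximation on log counts:

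- SD of the within-person log ratio D = 0.775 × √(2 × (1 − 0.2)) = 0.980.
- n = ((1.960 + 1.282) × 0.980 / |ln 0.7|)² = 79.4, so 80. This agrees with the article.
- 80 / 0.90 = 88.9, so 89; the article rounds up to 90.
- Power at n = 80 is Φ(0.3567 × √80 / 0.980 − 1.96) = 90.2%.

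The 10% allowance is for loss to follow-up only. Nothing is set aside for participants excluded because of unblinding.

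**Step 2: exclusion unrelated to outcome.** The ratio stays at 0.70. Power is Φ(0.3567 × √n / 0.980 − 1.96):

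| Excluded, of 80 evaluable | n left | Power |
|---|---|---|
| 10% | 72 | 87% |
| 20% | 64 | 83% |
| 30% | 56 | 78% |
| 50% | 40 | 63% |

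**Step 3: exclusion that follows benefit (assumed).** Take D ~ N(ln 0.7, 0.980) and remove only participants with at least 50% fewer events on SNM.

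- Share qualifying: Φ((ln 0.5 − ln 0.7) / 0.980) = Φ(−0.343), about 36.5%. Their mean D is −1.365.
- If a share f of all participants is removed at random from this group, the remaining mean is (−0.3567 + 1.365 f) / (1 − f).
- f = 0.10: (−0.3567 + 0.1365) / 0.90 = −0.245, ratio 0.78.
- f = 0.20: (−0.3567 + 0.2730) / 0.80 = −0.105, ratio 0.90.
- The ratio reaches 1 at f = 0.3567 / 1.365, about 26%.

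Simulation with 2,000,000 draws gives the same ratios, with power of 58% at f = 0.10 and 15% at f = 0.20.

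**Step 4: exclusion of large contrasts in either direction (assumed).** The same simulation, removing the largest values of |D|, gives ratios of 0.79 with 10% excluded, 0.84 with 20%, 0.89 with 30% and 0.94 with 50%. The ratio moves towards 1 but does not pass it.

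The excluded shares in Steps 2 to 4 are assumptions, because the article gives no unblinding rate for faecal incontinence.

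**The case against.** A reader might infer that the rule selectively removes responders and could push the estimate past 1. The documents do not support that as a statement of fact, for these reasons:

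- **Meaning of the term.** Perceived allocation is collected separately, as a measure of blinding success, which suggests that a correct guess need not count as being unblinded. If the rule means actual disclosure, exclusion need not depend on response, and Step 2 applies.
- **Evidence on frequency.** The 75% correct identification cited in the Discussion comes from an irritable bowel syndrome study. The article presents identification through symptoms as a risk, and it calls the effect size uncertain.
- **Mechanism in Step 3.** It selects on the contrast between the two 4-week diaries, which is complete only at week 32, whereas recognition would build up earlier. If month-to-month variation is independent within a person and everyone has the same proportional benefit, an earlier symptom contrast says nothing about D and excluding on it causes no bias. Bias needs variation that persists across months or benefit that differs between people, and the article quantifies neither.
- **Passing 1.** With a true ratio of 0.70 this needs nearly one-sided removal of about 21% of participants (strongest responders first) to 26% (at random among those with at least 50% fewer events).
- **Expectancy.** The diary is patient-recorded. If unblinding altered reporting, part of a shift towards 1 could be removal of bias.
- **Broken tape.** The Blinding procedures section says "The patient will not be removed from the study if the tamper-proof tape has been broken". That concerns staying in the study, and the Discussion also continues assessments, so the tension is weak.

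These points limit what can be claimed about the direction and size of bias. They do not resolve the contradiction. The Discussion does concede incomplete intention-to-treat, but only for selection from test stimulation onwards, which does not cover this exclusion.

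**Conclusion.** The contradiction stands and concerns who is in the primary analysis, so it needs correcting. The rule departs from the stated intention-to-treat principle whatever the route of unblinding.

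The consequence is conditional. If unblinding is unrelated to outcome, the cost is power alone: about 83% with 20% excluded and 78% with 30%, against a planned 90%. If it follows symptom benefit, the ratio is probably biased towards 1 by an unknown amount. The move from 0.70 to about 0.78 with 10% excluded shows the scale under one assumed mechanism and is not an expected value. All figures use the article's planning SD and correlation and a log-normal approximation to the planned mixed Poisson model.

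**What to change.** Delete the sentence in the Discussion. In the primary analysis section, state that all randomised participants with crossover diary data are analysed by allocated sequence, whatever their unblinding, tape status or guess of allocation.

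Define what counts as unblinding and keep it distinct from perceived allocation. Record its date and route on the case report form. Confine any exclusion of unblinded participants to a sensitivity analysis, reported by route where numbers allow, so that disclosure can be separated from recognition through symptoms.

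The cost is a small text change and a case report form item for the date and route. With these participants kept, the planned 80 evaluable and 90 randomised stand, and no extra participants are needed.

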### Cohort follow-up study

The primary study (double-blind crossover) will provide a robust estimate of experimental efficacy. The cohort of thus recruited patients, however, also provide an opportunity to study the outcome at a later time point with patient-decisive stimulation (sub- or supra-sensory) as would be normal for routine clinical practice. On this basis, patients will be followed up for a further 6 months to a total, therefore, of just over 1 year post implant (2 × 16 + 26 = 58) and outcomes recorded between 54 and 58 weeks (± 1 week). Such data will provide the first estimate of the outcome of optimised (internationally standardised) lead placement [25, 26] in adults with FI and also do so with the scientific rigor mandated by a prospective randomised study managed by a CTU (even if the intervention by this stage is ‘open label’). It is acknowledged that patients will only have actually had 36 weeks of stimulation (continuous or discontinuous depending on crossover sequence). However, published data indicate that outcomes at 6 months are almost identical to those at later time-points (accepting data censorship in some cohort studies).

### Trial registration

The trial is registered on a publically accessible registry: ISRCTN98760715 (Registered on 25 September 2017); http://www.isrctn.com/ISRCTN98760715.

### Trial status

The trial commenced recruitment in October 2017 and will take 18 months to recruit 90 patients. Recruitment milestones will be closely monitored.

## Abbreviations

AE: Adverse event
CI: Chief investigator
DMEC: Data Monitoring and Ethics Committee
EQ-5D-5 L: EuroQol Health Outcome Measure
FI: Faecal incontinence
FI QoL: Faecal Incontinence Quality of Life
GP: General practitioner
HRA: Health Research Authority
MEG: Magnetoencephalography
MRI: Magnetic resonance imaging
NICE: The National Institute for Clinical Excellence
OAB Q: Assessment of OverActive Bladder Symptoms
PCTU: Pragmatic Clinical Trials Unit
QoL: Quality of life
R&D: Research & Development
RCT: Randomised controlled trial
REC: Research Ethics Committee
SAE: Serious adverse event
SF-ICQ-B: International Consultation on Incontinence Bowel Questionnaire
SNM: Sacral neuromodulation
SOP: Standard operating procedure
TMG: Trial Management Group
TSAR: Transient Anal Sphincter Relaxations
TSC: Trial Steering Committee
